## Abstract

**Background:**

Pro Kind is a German adaptation of the US Nurse Family Partnership program. It is an intervention based on home visits targeting first-time mothers from disadvantaged populations. Pro Kind was implemented as a randomized control trial from 2006 to 2012 with *N* = 755 first-time mothers (TG *n* = 394, CG *n* = 391). The 7–8-year follow-up aims to assess the mid-term effects of the program.

**Methods/design:**

Mid-term outcomes are being assessed by trained assessors. In a multimethod approach telephone interviews, on-site interviews, observations and developmental tests will be held in order to assess children’s and mothers’ life satisfaction, mental health, cognitive and social development, parenting behavior, signs of child abuse or neglect as well as the family’s socio-economic status. Furthermore, administrative data will be accessed to obtain information regarding the mother’s usage of pediatric health care, welfare usage and employment history.

**Discussion:**

Results regarding the mid-term effects of the intervention from the Pro Kind Follow-up will provide a scientific basis for future primary prevention programs as well as help stakeholders legitimizing early childhood investments.

**Trial registration:**

German Clinical Trial Registration DRKS-ID, ID: DRKS00007554. Registered on 11 June 2015, updated on 6 October 2017.

**Electronic supplementary material:**

The online version of this article (10.1186/s13063-018-2707-3) contains supplementary material, which is available to authorized users.

## Background

Based on international research findings, home-visiting programs appear to be a promising approach to support psychosocially and/or economically disadvantaged families. Several meta-analyses show that early prevention programs improve parenting skills, reduce child maltreatment and neglect, and have a positive effect on the child’s development [1–8]. Although home-visiting programs have a long tradition in Europe [9], the predominant scientific findings stem from the United States (US), especially from the *Nurse Family Partnership Program* (NFP; [10]). Within the NFP framework, disadvantaged mothers receive close support already before the birth of their first child. The home visits continue up to the child’s second birthday. NFP supports maternal parenting skills relating to the positive support of the child’s emotional, cognitive and social development. Furthermore, child neglect, child maltreatment and child abuse are prevented. By reducing the consumption of alcohol and nicotine, NFP promotes the mother’s health-related behaviors during pregnancy. In addition, the program encourages mothers (or the parents) to expand their formal and informal networks. Finally, the program aims to enable the families to gain financial autonomy and hence independence from unemployment benefits and welfare. To evaluate the NFP program three randomized controlled trials (RCTs) were conducted in 1977, 1988 and 1994 in the three different US populations in Elmira, NY; Memphis, TN; and Denver, CO. In numerous articles these RCTs reported positive effects regarding the mothers’ health-related behavior during pregnancy, the child’s health, parental skills, the socio-emotional and cognitive development of the child, as well as the integration of the mother into the job market or her willingness to take up educational offers. In the long term, better social integration, lower crime rates and improved labor market outcomes were found for children from families who participated in the NFP program [11–30]. According to current estimates (see [31]), approximately 500 child deaths, 4700 abortions, 36,000 cases of partner violence, 90,000 violent crimes by juvenile offenders, 594,000 cases of property crimes or public order disturbances (e.g., vandalism, damage to property), 36,000 prison terms and 41,000 cases of youth substance abuse will have been prevented by NFP in the US by the year 2031. Two independent US research groups conducted comprehensive cost-benefit analyses of NFP. The first analysis, by the Rand Corporation, calculated net returns of US$2.88 for every dollar invested – the returns were greater for the highest-risk families, for which they nearly doubled [32]. The second analysis, by the Washington State Institute for Public Policy, estimated a return of over US$17,000 for every family [33]. Both evaluations factored in the cost savings across several public sectors over 10–15 years, including reduced health care, income assistance and child protection spending. Notably, averted public expenditures were greatest for the most disadvantaged mothers and children, which highlights the importance of offering NFP to those at higher risk [34]. In conclusion, the public savings by NFP in the US (as of 2010) are estimated to be approximately US$1.5 billion [31].

Trials of NFP have also been conducted outside the US (currently, there are also trial registrations for Canada [35] and France [36]). In the Netherlands, a trial that compared NFP to existing health and social services found that it reduced prenatal smoking, increased breastfeeding, reduced the number of child protection reports as well as the incidence of partner violence [37–39]. In contrast, an RCT in England that compared NFP (called FNP) to usual health and social services did not find any additional benefits for either the children or their mothers [40]. These differences in the findings of US, Dutch, and English trials emphasize the necessity of carrying out RCTs in further countries outside of the US before implementing NFP on a larger scale. Results from RCTs would assess the program’s effectiveness as compared to services that are already in place for the target population [41].

### NFP in Germany: The “Pro Kind” study

In Germany, within the framework of the model project Pro Kind, a German adaptation of the NFP program has been scientifically evaluated since 2006. The core components of the NFP interventions were implemented by the Pro Kind program without changes, including the target group criteria, the specified average number of visits and the average duration of a visit. Furthermore, the structured procedure as well as the support for the home visitors through supervision accord with the US original. Modeled after the NFP program, the home visitors conducted the visits regularly, from pregnancy to the child’s second birthday. Diverging from the original program, in the German adaptation home visits were carried out by social workers and state licensed midwives either alone (mainly midwives) or in tandems of a midwife and a social worker (see [42]), whereas in the NFP program exclusively nurses were engaged as home visitors.

### Domains addressed in the Pro Kind intervention

Six focus areas (domains) are addressed while working with the participants in the intervention setting. These domains are generally regarded as the most important risk and protective factors for the prevention of negative pregnancy outcomes, child abuse or neglect, developmental retardation and limited economic independence.Personal health of the mother. Central in this domain is support during pregnancy. Health-related behavior of the expecting mother is addressed such as nutrition, exercise, sleep and rest, as well as oral hygiene. Furthermore, tobacco and alcohol consumption are covered within this domain. Additionally, pregnancy-related physical changes as well as childbirth are discussed.Healthy environment. In this domain the setup of the home environment for parent and child is addressed. Focus aspects are child safety and accident prevention. Toxic or hazardous aspects of the home environment, such as mold and indoor smoking, are also covered.Personal plans for the future. The timing and other considerations of returning to the job or education are the focus of this domain. In this context family planning also plays an important role. Individual preferences, as well as personal strength and weaknesses of the mother, are explored and taken into account for the development of realistic perspectives. Additionally, aspects of everyday personal management, for example, regarding time and money are addressed within this domain.Maternal/ paternal/ parental role. This is the focal domain between birth and the child’s second birthday. But even during pregnancy, parents are sensitized to the basic needs of a child as well as child development in utero. Fears and expectations regarding the life with a child are also addressed. Post-partum baby care and nutrition as well as basic needs of a newly born are covered. Later developmental and educational aspects (i.e., media exposure), as well as stimulation of the parent-child interaction, are important features of this domain.Social network. Social support from the partner, the parents or friends are aspects in this domain. Building interfamilial relationships and friendships as well as falling back on those for everyday support are supported. On the other hand, resolving conflicts, and appropriate non-violent communication between partners are covered.Utilization of social as well as health services. Aspects from this domain are usually covered in case of acute necessity as well as for establishing a general network of support. Examples are check-ups during pregnancy, check-ups for the child or mother-child playgroups or classes. Additionally, mothers are supported in the arrangement or accompanied to official appointments. In cases of psychiatric illness, developmental problems of the child or domestic abuse contact with the relevant social, medical or legal services is facilitated.

### Methodological starting point of the Pro Kind project

#### Sample and sampling

The Pro Kind program was conducted from 2006 to 2012 in the three German states Bremen, Lower Saxony and Saxony (funded by the German Federal Ministry for Family Affairs, Senior Citizens, Woman and Youth BMFSJ [funding code: IIA6-25080820 V6], the Günter-Reimann-Dubbers Foundation [no funding code available], the Dürr Foundation [no funding code available], and the TUI Foundation [no funding code available]; the principal investigator of the intervention phase was TJ). The program was evaluated via longitudinal assessment [43] up to the children’s third birthday within the framework of a multicenter RCT. At the time of the baseline survey, *N* = 755 first-time mothers (TG *n* = 394, CG *n* = 391) participated, who were 12 to 28 weeks pregnant. In addition to first-time pregnancy the inclusion criteria were a financial risk factor (e.g., receiving welfare benefits or being in debt), as well as at least one further social or personal risk factor (e.g., being under age, lack of a school leaving certificate, having experienced abuse or neglect). In an a priori power analysis before the original RCT the sample size was estimated to be *N* = 775. We assumed (1) a minimum detectable effect sizes of ES = 0.20 (i.e., small effect), (2) a type I error rate (false positive) of α = .05, (3) statistical power (1 − *β*) of .80 (where *β* is the probability of making a Type II error, i.e., failing to detect a true effect if it is present) and (4) an attrition rate of 25% for this estimation.

The participants were recruited through various multipliers – especially through gynecologists, midwives, youth welfare offices, psychosocial counseling centers, and employment agencies [44]. After admission to the model project, those who at the time were between 12 and 28 weeks pregnant were randomly allocated to either the study group or the control group via a computer program (Efron’s biased coin design, strata: implementation location, being under age, and nationality of the mothers). Both groups had access to the regular support offered by the German welfare system and were informed about the latter. Furthermore, travel expenses to medical check-ups during as well as after pregnancy were covered as part of the panel maintenance. In addition, compensation was paid for the time participants invested for the program assessment.

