#### Program participation

As in the original NFP program, Pro Kind participation was voluntary. It is, hence, evident that not all mothers in the experimental group stayed in the program up to the child’s second birthday and hence not all program contents could be covered as intended. In all, *n* = 166 (42.2%) of the *n* = 394 randomized mothers in the experimental group dropped out of the intervention prematurely. The reasons for termination can be divided into endogenous and exogenous causes. Endogenous termination causes can be understood as those that were caused deliberately and directly by the mother (e.g., through an explicit demand to terminate the program) or indirectly (e.g., by cutting off contact). Conversely, exogenous termination causes can be understood as those caused by external circumstances (e.g., the child being taken into custody by the youth welfare office, sudden death of the child, relocation of the mother to an area where no further home visits could be provided) and hence not deliberately caused by the mother. During the first intervention phase (before the birth of the child) *n* = 52 mothers terminated the program prematurely; hereof, *n* = 38 (73.1%) terminations can be regarded as endogenous terminations. During the second intervention phase (after birth up to the child’s first birthday) *n* = 87 additional mothers dropped out of the intervention. Of these, *n* = 48 (55.2%) can be regarded as endogenous terminations. During the last intervention phase (from the child’s first to second birthday) only 27 more mothers did not complete the program as intended; *n* = 17 (63.0%) due to endogenous termination causes.

Altogether, the families received an average of *M* = 32.7 home visits (*SD* = 18.6) with a range of 0 to 94 home visits. If only those families that completed the program are considered as intended, there was an average of 45.3 home visits (*SD* = 19.7) ranging from 11 to 94 home visits. Across all families, approximately 13,000 home visits were conducted within the Pro Kind project. The average length of a home visit was 82 min. In conclusion, the length of the home visits, as well as the frequency among those families that completed the program, are comparable to those of the US original.

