### Data analysis

The primary and secondary analyses will be conducted on an intention-to-treat basis. Multilevel modeling will be used for statistical analyses of our primary and secondary outcomes. Prior to analysis, data will be checked for outliers, inconsistencies and possible transformation. We predict that our sample size will be large enough for our statistical tests to be robust regarding non-normally distributed variables. To reduce bias and loss of statistical power in our analysis of primary and secondary outcome indicators, we will use multiple imputations to estimate values for missing data. Power analyses (i.e., *sensitivity*) based on an attrition rate of 30% (*N* = 542 for the CATIs, CAPIs and developmental tests) given a type I error rate (false positive) of α = .05 and statistical power of 1− *β* = .80 resulted in a minimum detectable effect sizes of ES = 0.2. For an attrition rate of 40% (*N* = 465) a minimum detectable effect sizes of ES = 0.23 was estimated. To take that into account we analyze different outcome measures within one hypothesis, we will adjust our results for multiple hypothesis testing (MHT) to control the family-wise type I error rate.

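### The stated total (755) and the arm sizes (394 + 391 = 785) contradict each other, and the follow-up sizes rest on a third, unnamed base (775)

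*Protocol article*

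**What the plan says.** The sample is counted in several places in the protocol article.

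- Abstract, Background: "N* = 755 first-time mothers (TG *n* = 394, CG *n* = 391".
- Sample and sampling, for the baseline survey: "N* = 755 first-time mothers (TG *n* = 394, CG *n* = 391) participated".
- Program participation, for the intervention arm alone: "n* = 166 (42.2%) of the *n* = 394 randomized mothers in the experimental group".
- Sample and sampling, for the planned size: "In an a priori power analysis before the original RCT the sample size was estimated to be *N* = 775".
- Data analysis, for the follow-up: power is "based on an attrition rate of 30% (*N* = 542 for the CATIs, CAPIs and developmental tests", with a minimum detectable effect of 0.2. For 40% attrition it gives N = 465 and 0.23.

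The Data analysis section commits the primary and secondary analyses to intention to treat, with multiple imputation for missing data. It gives neither the number randomised nor the base to which the attrition rates were applied.

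**The concern.** The two arms do not sum to the total printed beside them. The mismatch appears identically in the abstract and the methods, so a text-extraction fault is an unlikely explanation. The follow-up sizes then point to a third number that is neither the printed total nor the sum of the arms.

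Intention to treat and attrition both need the number randomised in each arm. The Limitations section warns that selective data loss can distort the effect estimates, and a reader can judge that only with a firm denominator per arm. If the uncertainty lies in the control arm, its size is 391 or 361, and the 30 mothers are 7.7% or 8.3% of it. As an illustration with an assumed count, 250 control mothers followed up would be 63.9% of 391 or 69.3% of 361.

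**Working it through.** **Step 1. Total against arms** (Abstract; Sample and sampling).

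- 394 + 391 = 785, and 785 − 755 = 30.
- If 755 and 394 are right, the control arm is 755 − 394 = 361.
- If 755 and 391 are right, the intervention arm is 755 − 391 = 364.
- If both arms are right, the total is 785.

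**Step 2. Which figure is the likelier slip** (Program participation).

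- That section repeats 394 as the number randomised to the intervention.
- Its phase-specific terminations sum to its stated total: 52 + 87 + 27 = 166.
- Mean visits times arm size: 32.7 × 394 = 12,884, which fits the stated figure of roughly 13,000. With 364 mothers it would be 32.7 × 364 = 11,903.
- One small blemish: 166/394 = 42.1%, whereas 42.2% is printed (166/393 = 42.2%).

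On balance 394 is supported, which leaves the total or the control arm. Nothing in the document decides between these two.

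**Step 3. Reproducing the printed follow-up sizes.**

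- 775 × 0.70 = 542.5, printed as 542.
- 775 × 0.60 = 465, printed as 465.

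The base is therefore the planned 775.

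**Step 4. The same rates on the two candidate enrolled totals** (halves rounded down, as the article does with 542.5).

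| Base | 30% attrition | 40% attrition | Attrition implied by 542 | Attrition implied by 465 |
|---|---|---|---|---|
| 755 | 528 | 453 | 1 − 542/755 = 28.2% | 1 − 465/755 = 38.4% |
| 785 | 549 | 471 | 1 − 542/785 = 31.0% | 1 − 465/785 = 40.8% |

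The largest gap from the printed sizes is 542 − 528 = 14 participants (14/542 = 2.6%).

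**Step 5. Effect on the minimum detectable effect (MDE).** MDE = 2(z_α + z_0.80)/√N, with equal allocation (assumed), α = .05 and power .80. The article does not state whether the test is one- or two-sided, so both are shown.

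| N | Source | One-sided | Two-sided |
|---|---|---|---|
| 542 | printed, 30% | 0.214 | 0.241 |
| 528 | 755, 30% | 0.216 | 0.244 |
| 549 | 785, 30% | 0.212 | 0.239 |
| 465 | printed, 40% | 0.231 | 0.260 |
| 453 | 755, 40% | 0.234 | 0.263 |
| 471 | 785, 40% | 0.229 | 0.258 |

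Within either column, changing the base moves the MDE by about 0.003 to 0.004 at most. The one-sided values round to the printed 0.2 and 0.23 on every base.

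**The case against.** The strongest defence is that this is a misprint in an article. Allocation was done by computer program, so the study team should know who was randomised, and no analysis in the text uses 755 or 785 as a number. That stands as far as it goes: the contradiction does not show that the intention-to-treat population itself will be wrong. It shows that the reader cannot tell what that population is.

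It could also be said that 755 counts baseline participants and 785 those randomised. The text does not draw that distinction. It prints the arm sizes as the breakdown of 755, and the abstract gives the same trio as the size of the trial.

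Three stronger readings are tempting, and the document does not support them.

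- **The follow-up sizes are wrong.** They follow exactly from 775 and lie between the values from 755 and 785. A planned size that differs from enrolment is not an error. The fault is that the base is not named and matches neither enrolled total. They would be right if 775 had been enrolled, but the document labels 775 only as the target, and with 394 it would need a control arm of 381, which is printed nowhere.
- **The count error explains why two-sided MDEs of about 0.24 to 0.26 exceed the printed 0.2 and 0.23.** It does not. At the printed 542 and 465 the two-sided values are already 0.241 and 0.260. That gap is almost wholly a matter of sidedness, which is a separate issue.
- **The control arm is misstated by 30 mothers.** That is one of two likely explanations. If 755 is the slip, both arms are right.

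**Conclusion.** The contradiction is certain: 755 and 394 + 391 cannot all be correct, and the number randomised cannot be recovered from the document. That 394 is sound is a reasonable inference from the program participation figures, not a proof. That the attrition rates were applied to 775 is an inference from an arithmetic match at both rates.

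The discrepancy is 30 mothers in the total. The follow-up sizes shift by at most 14 participants, and the effect on power is negligible. Design, analysis method and power conclusions are unaffected by the choice of base. It still merits correction, because the number randomised per arm is the denominator for every attrition and intention-to-treat statement that will follow.

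**What to change.** 1. Check the randomisation list and state the number randomised in each arm.
2. Correct the total or the arm size in both the abstract and the Sample and sampling section. If 755 and 785 count different things, such as baseline participants and mothers randomised, say so.
3. In the Data analysis section, name the base and apply the 30% and 40% attrition to the number actually randomised: 528 and 453 if 755, 549 and 471 if 785. Restate the minimum detectable effects on that basis.
4. Use the corrected arm sizes as denominators when attrition is reported by arm.

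The registry record was not available for this review, so there is no ground to say that it carries the error; it can be compared with the list at the same time.

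The cost is one look-up and a few corrected figures, with no change to design, data collection or analysis method.

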#### Program participation

As in the original NFP program, Pro Kind participation was voluntary. It is, hence, evident that not all mothers in the experimental group stayed in the program up to the child’s second birthday and hence not all program contents could be covered as intended. In all, *n* = 166 (42.2%) of the *n* = 394 randomized mothers in the experimental group dropped out of the intervention prematurely. The reasons for termination can be divided into endogenous and exogenous causes. Endogenous termination causes can be understood as those that were caused deliberately and directly by the mother (e.g., through an explicit demand to terminate the program) or indirectly (e.g., by cutting off contact). Conversely, exogenous termination causes can be understood as those caused by external circumstances (e.g., the child being taken into custody by the youth welfare office, sudden death of the child, relocation of the mother to an area where no further home visits could be provided) and hence not deliberately caused by the mother. During the first intervention phase (before the birth of the child) *n* = 52 mothers terminated the program prematurely; hereof, *n* = 38 (73.1%) terminations can be regarded as endogenous terminations. During the second intervention phase (after birth up to the child’s first birthday) *n* = 87 additional mothers dropped out of the intervention. Of these, *n* = 48 (55.2%) can be regarded as endogenous terminations. During the last intervention phase (from the child’s first to second birthday) only 27 more mothers did not complete the program as intended; *n* = 17 (63.0%) due to endogenous termination causes.

Altogether, the families received an average of *M* = 32.7 home visits (*SD* = 18.6) with a range of 0 to 94 home visits. If only those families that completed the program are considered as intended, there was an average of 45.3 home visits (*SD* = 19.7) ranging from 11 to 94 home visits. Across all families, approximately 13,000 home visits were conducted within the Pro Kind project. The average length of a home visit was 82 min. In conclusion, the length of the home visits, as well as the frequency among those families that completed the program, are comparable to those of the US original.

